### Outcome measures

#### Primary outcome

The primary outcome measure will be the total score of the German version of the SASKO [27] measured at baseline assessment and post assessment (post-assessment–baseline assessment). The SASKO is a self-report questionnaire that contains the symptoms of SAD. It has four subscales: (1) anxiety of speaking and being in the center of attention (12 items), (2) fear of rejection (10 items), (3) interaction deficits (10 items), and (4) information processing deficits (8 items) and a total score (40 items). All items are judged on a 4-point Likert scale ranging from 0 (“never”) to 3 (“always/most of the time”). It has a high internal consistency (Cronbach’s *α* = .92) and good validity [27]. Participants will be presented with the SASKO at four time points. These time points are the baseline assessment (around 2 weeks after enrollment), interim assessment (6 weeks after baseline), post-assessment (10 weeks after baseline), and follow-up assessment (16 weeks after baseline).

#### Secondary outcome

Remission will be used as a clinically relevant outcome. Remission will be assessed by the Mini-Dips [24], a reliable (Kappa = .94 for anxiety disorders) and valid instrument, that is often used in clinical studies [30], on follow-up assessment (16 weeks after baseline).

#### Exploratory variables

Effects of the treatment on additional clinically relevant measures (e.g., anxiety, depression, control beliefs, etc.), as well as the role of potential moderators/mediators, will be tested in exploratory analyses. Therefore, the following measures will be obtained at all four-time points: (1) the Questionnaire on Beliefs in Competency and Control (FKK) [31], (2) the German version of the Center for Epidemiological Studies Depression Scale (ADS) [32], (3) Positive Mental Health (PMH) [33], and (4) the German version of the University of Rhode Island Change Assessment Scale (URICA) [34]. At baseline, (1) the State-Trait-Anxiety-Inventory (STAI) [35] and (2) the Anxiety Sensitivity Index (ASI-3) [36] will be applied. They will only be filled in once because of the stability of the measures. The detailed procedure of measurements is listed in the schedule of enrollment, intervention, and assessment (Fig. 2).

#### Ethics statement

The study protocol (10/2021) was approved by the Ethics Committee of the University of Siegen (reference number: ER_84_2021). The study was designed in accordance with the Declaration of Helsinki, Good Clinical Practice guidelines, and the SPIRIT reporting guidelines. During the run of the study, ethical, legal, and social aspects will be anticipated and addressed. Participants will provide written informed consent to the experimental procedure prior to inclusion in the study. Participation will be entirely voluntary, and participants will have the right to withdraw their consent at any time. Data will be pseudonymized with a trial identification number. It will be saved on a secure, self-encrypting database and can only be accessed by the responsible researchers. Participants will not be financially compensated for their participation in this low-risk intervention. No major adverse events are anticipated. Yet, as a minor anticipated event, motion sickness because of virtual reality is possible. In case of any unforeseen adverse events or a deterioration of symptoms, participants will have the opportunity to talk to their therapist, who will then initiate necessary care steps.

#### Randomization and blinding

Participants will be randomly assigned to the experimental or the control group by a 1:1 allocation ratio. A computer-generated randomization scheme was implemented via R 4.1.1. Permuted block randomization will be used to ensure that both groups include 20 participants. Due to the study design, it is not possible to blind the participants or the psychotherapists after the allocation. Participants will be assigned to the interventions by the therapists. To avoid bias during data assessment and analysis, research assistants concerned with enrollment and data analysis will be blind to participants’ group allocations.

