## Methods and materials

### Procedure

#### Screening

To pre-select the participants, a screening via telephone will be used, including SAD symptoms as outlined in the Mini-DIPS and inclusion and exclusion criteria. Participants that do not fulfill the criteria will be excluded and offered to be put on the waiting list of the Outpatient Center for Psychotherapy of the University of Siegen. The screening will be conducted by research assistants, trained by a psychotherapist. If participants fulfill the inclusion criteria, they will be invited to a first appointment with a certified psychotherapist.

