#### Second appointment (baseline assessment)

At a second appointment (around 100 min), a structured clinical interview, the Mini-DIPS, will be conducted by a psychotherapist to verify the diagnosis of SAD, to explore comorbid psychological disorders, and to test for psychological disorders leading to exclusion from this study. If eligible for participation, patients will be assigned to the experimental group (EG) or the control group (CG) according to a computer-generated randomization scheme and participate in an online survey, conducted by trained research assistants. Afterwards, patients randomized to the EG will receive their prescription for the application (Invirto 1.17.0, Sympatient, Hamburg; class I after the Medical Device Directive 93/42/EWG [29]). The EG will be asked to start the intervention, while the CG will be asked to wait until the next appointment.

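### Psychotherapists judge final eligibility, assign the arm and are unblinded under permuted blocks, so allocation concealment is not secured as written

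*Protocol article*

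**What the plan says.** The relevant statements are in four sections of the protocol article.

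- **Screening.** The telephone pre-selection is done by assistants: "The screening will be conducted by research assistants, trained by a psychotherapist".
- **Second appointment (baseline assessment).** The deciding check comes here: "the Mini-DIPS, will be conducted by a psychotherapist to verify the diagnosis of SAD". The same interview serves "to test for psychological disorders leading to exclusion from this study". Assignment follows at that appointment: "If eligible for participation, patients will be assigned to the experimental group (EG) or the control group (CG) according to a computer-generated randomization scheme". The online survey is named after the assignment, in the same sentence. The application is prescribed to the experimental group after that.
- **Randomization and blinding.** On who assigns: "Participants will be assigned to the interventions by the therapists". On the method: "Permuted block randomization will be used to ensure that both groups include 20 participants". On blinding: "it is not possible to blind the participants or the psychotherapists after the allocation". The only people described as blind are the research assistants concerned with enrolment and data analysis. The scheme was generated in R with a 1:1 ratio. No block size is given.
- **Participants.** One outpatient centre is named.

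**The concern.** Randomisation protects the comparison only if whoever decides on inclusion cannot foresee the next arm. Here the article gives the final inclusion decision and the assignment to the same role, and people in that role know the arms of patients they have treated. The stated safeguard does not reach this step, because it protects research assistants, whose part in eligibility is the telephone pre-screen.

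There is some room for influence, which need not be deliberate. By the second appointment the therapist has already spent a 100-minute session on motivation, symptoms and history, so a view of prognosis is possible. Several criteria call for judgement, such as whether social anxiety disorder is the primary disorder and whether depression is severe. Control patients receive the application only after the follow-up at 16 weeks, so a preference about who should wait is plausible.

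The order of events raises a second issue. The primary outcome is the change in self-reported SASKO total score from baseline to post-assessment. If the baseline survey is filled in after assignment, and the patient knows the arm by then, the arm can colour one of the two scores that form the outcome.

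With 20 patients per arm, a few steered inclusions could shift the comparison for both the primary and the secondary outcome.

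**Working it through.** The plan gives no figure for predictability, so there is none to reproduce. The check has two parts.

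**1. Who does what, and when**

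| Step | Done by | Blind to allocation? |
|---|---|---|
| Telephone pre-screen | Research assistants | Yes, if concerned with enrolment |
| Mini-DIPS: diagnosis and exclusions | Psychotherapist | Not to allocations already made to own patients |
| Assignment to arm | Therapists | No |
| Baseline online survey, listed after assignment | Research assistants | Stated only for those concerned with enrolment and data analysis |

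The second and third rows fall to the same role at the same appointment. The article describes no separation between them.

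**2. How many allocations could be foreseen**

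Inputs from the article: 40 patients, 1:1 ratio, permuted blocks. Assumptions that are not in the article: all blocks have one fixed size 2m, the therapist knows that size, and the therapist has seen every earlier allocation.

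An allocation is fully determined once the other arm is used up within its block. Each of the m places for one arm falls after all m places of the other arm with probability 1/(m + 1). Summed over both arms, the expected number determined per block is 2m/(m + 1). As a share of the block this is 1/(m + 1), and over the trial it is 40/(m + 1).

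The second measure is the share of correct guesses when the therapist always names the arm with more places left. For a block of 4, the chance of a correct guess is 1/2 at the first place and 2/3 at the second. At the third it is 1/3 × 1 + 2/3 × 1/2 = 2/3, and at the fourth it is 1. The sum is 2.833, and 2.833/4 = 70.8%. The other sizes were enumerated exactly in the same way.

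| Block size | m | Share determined | Determined out of 40 | Correct guesses |
|---|---|---|---|---|
| 2 | 1 | 1/2 = 50% | 20.0 | 75.0% |
| 4 | 2 | 1/3 = 33.3% | 13.3 | 70.8% |
| 8 | 4 | 1/5 = 20% | 8.0 | 66.6% |
| 10 | 5 | 1/6 = 16.7% | 6.7 | 65.3% |
| 20 | 10 | 1/11 = 9.1% | 3.6 | 61.7% |
| 40 | 20 | 1/21 = 4.8% | 1.9 | 58.7% |

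The sizes shown divide 40 evenly. With full concealment and no knowledge of past allocations, the guess rate is 50%.

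**The case against.** A reader might infer that therapists know the whole sequence and so do anticipate allocations. The documents do not support that. They say only that therapists cannot be blinded after allocation, which is unavoidable when they deliver the condition. The number of therapists is not given, nor is whether one sees another's allocations. The block size is not given, nor is it said to be fixed or known to them. A therapist who knows only the arms of their own patients cannot in general reconstruct a block for the whole centre. This stands, and it is why the figures above are conditional. It also rules out a claim that 10 or more patients are affected: that holds only for small blocks, and the number falls to about 2 with one block of 40.

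The sentence on assignment by therapists may mean only that they carry out an allocation from a concealed list, since the second-appointment section refers to a computer-generated scheme. The full protocol may say so, and block size is a detail that an article may leave out. This stands in part. Silence on block size is no fault. What the article does state, however, is that the role judging eligibility also assigns, and it places its blinding elsewhere.

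The therapist's discretion is bounded. Criteria are first applied by telephone, and the interview is structured, with a stated Kappa of .94 for anxiety disorders. Bounded discretion is still discretion.

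The planned analyses can adjust for measured group differences, so it would be too strong to say that nothing can be done in analysis. Adjustment does not remove selection on unmeasured prognosis.

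On the survey, the article's sentence may list events without fixing their order, and it does not say that patients already know their arm when they answer. A reader might infer that baseline scores are contaminated, but the text shows only that nothing prevents it.

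**Conclusion.** The point holds as a weakness in the stated procedure. Psychotherapists make the final eligibility check, assign the arm and are unblinded after allocation, and the blinding described protects a different group. The listed order also allows baseline self-reports to follow assignment.

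This is a risk. Neither the direction nor the size of any bias is shown. If a therapist saw all earlier allocations and knew a fixed block size, about 2 to 20 of 40 allocations would be fully determined, and 59% to 75% would be guessed correctly. With varying blocks, or with several therapists who do not share information, the numbers would be lower. If the list is in fact held and released by someone else, a sentence saying so settles the question of who controls it. Therapists might still infer the end of a block if sizes are fixed and can be guessed.

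**What to change.** - **Randomization and blinding.** State that an existing team member with no role in eligibility or treatment holds the R list. That person releases one allocation at a time, only after eligibility is recorded and the baseline survey is complete. Therapists then only carry out the assigned condition.
- **Block sizes.** For any patients still to be randomised, use varying block sizes that are not disclosed to therapists.
- **Second appointment (baseline assessment).** Reorder the text so that the baseline survey precedes assignment.

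The cost is one release step per patient by existing staff, and a possible departure from 20:20 by one or two.

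The trial status section has recruitment running from March 2022 to January 2024. If it has ended, report who held the list, which block sizes were used and whether the survey came before or after assignment, and limit the conclusions accordingly.

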#### Data preparation and planned analyses

Multiple imputations of missing data will be performed for intention-to-treat (ITT) analyses [37]. Application-based treatment effects on the primary and secondary outcome measures will be tested using variance analytic methods. Potential associations between exploratory as well as demographic variables and the factor group, as well as their associations with outcome-variables, will be explored. If adequate, analyses on treatment effects on primary and secondary outcomes will be recalculated, thereby controlling for potential confounding effects.

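### Covariates for the re-analysis are to be picked by their observed association with randomised group and outcome, from a pool not limited to baseline values, and the plan does not say which result governs

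*Protocol article*

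**What the plan says.** Under Data preparation and planned analyses, the protocol article first states that treatment effects on the primary and secondary outcomes will be tested by variance-analytic methods. It then sets out a two-step procedure. Step one: "Potential associations between exploratory as well as demographic variables and the factor group, as well as their associations with outcome-variables, will be explored". Step two: "If adequate, analyses on treatment effects on primary and secondary outcomes will be recalculated, thereby controlling for potential confounding effects". No covariate, time point or threshold is named, and nothing says whether the main or the recalculated analysis carries the conclusion.

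The pool is defined under Exploratory variables. For the FKK, ADS, PMH and URICA, "the following measures will be obtained at all four-time points", so three of their four values come after baseline. For the STAI and ASI-3, "They will only be filled in once because of the stability of the measures". The same section sets the purpose of the exploratory work: "Effects of the treatment on additional clinically relevant measures (e.g., anxiety, depression, control beliefs, etc.), as well as the role of potential moderators/mediators" are to be tested.

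Under Second appointment (baseline assessment), eligible patients are assigned "according to a computer-generated randomization scheme and participate in an online survey, conducted by trained research assistants". Allocation is thus mentioned before the baseline questionnaires. Randomization and blinding adds that participants cannot be blinded once allocated.

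**The concern.** A confounder is a common cause of exposure and outcome. Randomisation removes such causes by design, so a baseline variable can be related to group only by chance, and its relation to group says nothing about whether adjusting for it is useful. What makes a baseline covariate useful is its relation to the outcome, and that can be judged in advance. A screen that also requires association with group will discard good prognostic variables in almost every trial.

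After baseline the position reverses. A variable related to both group and outcome is then what an effective treatment would be expected to produce. Adjusting for it is not control of confounding; it subtracts part of the treatment effect. The procedure draws on a pool that includes such values and has no clause to keep them out.

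The covariate set would also be settled after group and outcome associations had been inspected, for the primary outcome as well as the secondary one, with no statement of which result counts.

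**Working it through.** The plan gives no figure on this point, so there is none to reproduce. The checks use its 20 per arm, α = 0.05 and d = 0.50 (Sample size), with the SASKO change score (Primary outcome) compared between two groups and scaled to a within-arm SD of 1. Covariate strengths and screening thresholds are assumptions. The plan's 80% power refers to a 2 × 4 repeated measures ANOVA; the powers below are a common reference for comparing covariate rules and do not test that figure.

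**1. True baseline covariates: power.** Assume one covariate with within-arm correlation r = 0.5 with the outcome.

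- Unadjusted: noncentrality = d·√(n/2) = 0.50 × √10 = 1.58, which gives about 34% power on 38 df.
- Adjusted: residual SD = √(1 − 0.5²) = 0.866, so the effective d = 0.50/0.866 = 0.577 and noncentrality = 0.577 × √10 = 1.83. This gives about 42% on 37 df once the small cost of estimating the slope is allowed for.

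Simulation agrees:

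| Rule | Mean effect | Rejection at d = 0.5 |
|---|---|---|
| Unadjusted | 0.50 | about 34% |
| Covariate fixed in advance | 0.50 | about 41% |
| Covariate kept only if p < .05 with group and with outcome | – | about 33% |

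The screen keeps the covariate in only about 4% of trials, so it almost never delivers the gain. In those trials the mean adjusted estimate is still about 0.50.

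**2. True baseline covariates: type I error.**

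| Pool and screen | Unadjusted | Significant in either analysis |
|---|---|---|
| 1 covariate, group and outcome, p < .05 | 5.0% | 5.1% |
| 10 covariates, group and outcome, p < .05 | 5.4% | 5.7% |
| 8 covariates, group only, p < .10 | 4.9% | 5.9% |

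For the first two rows, using the adjusted result whenever the screen selects something gives 4.3% and 4.2%. The third row screens on group alone, which is not quite the stated rule.

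**3. Post-baseline covariates, if used.** Let treatment shift the variable by a, and let the variable act on the outcome with slope b. The adjusted effect is then total − a·b.

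- Half mediated (a = 0.5, b = 0.5): 0.50 − 0.25 = 0.25. A group-and-outcome screen selects this variable in about 32% of trials at p < .05 and 46% at p < .10.
- Range with b = 0.6, screen at p < .05:

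| Shift a | Adjusted effect | Selected by screen | Rejection: unadjusted → adjusted |
|---|---|---|---|
| 0.3 | 0.50 − 0.18 = 0.32 | 16% | 34% → 23% |
| 0.5 | 0.50 − 0.30 = 0.20 | 35% | 34% → 11% |
| 0.8 | 0.50 − 0.48 = 0.02 | 69% | 34% → 5% |

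The more strongly treatment moves the variable, the more often the screen picks it and the more of the effect is removed.

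**The case against.** The strongest reply is that the paragraph describes a routine check of baseline imbalance. It pairs exploratory with demographic variables and speaks of confounding, the pool includes two questionnaires taken only at baseline, and covariate lists and thresholds are details that an article may leave to an analysis plan. This stands in part. Nowhere does the text say that post-baseline values will be covariates; it only fails to exclude them. The selection rule, however, is stated rather than missing, and it is unsound even on the baseline reading.

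A reader might go further in four ways, none of which the document supports.

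- *That the plan adjusts for variables it calls mediators.* It speaks only of potential moderators or mediators, assigns neither role to any questionnaire, and places that work in separate exploratory analyses.
- *That there will be two competing primary results.* The recalculation is conditional and stands beside the main analysis, which is not replaced. What remains true is that no order of precedence is given.
- *That the rule seriously inflates false positives.* Among true baseline covariates it hardly does, and nothing in the text says that significance in either analysis counts as success.
- *That adjustment could inflate or create an effect.* This can be made to happen, for example 0.50 becoming 0.80 if treatment moves a post-baseline covariate by 0.5 SD against benefit. It needs post-baseline values plus a further assumption that the document gives no reason to make.

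The fall from 0.50 to 0.25 also follows directly from assuming that half the effect is mediated. It shows how the damage would arise and does not forecast its size in this trial.

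**Conclusion.** The concern holds in a limited form. Selecting covariates by observed association with randomised group and outcome is a poor rule. With true baseline values its price is mainly forgone precision, about 33% against 41% power for one covariate with r = 0.5, plus an unresolved choice between two results. Bias and type I inflation are small. The larger harm, loss of the mediated part of the effect, depends on post-baseline values entering the model. The text leaves that open but does not announce it, and its size rests wholly on the assumed mediator strength.

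One further point bears on any remedy. Because allocation is mentioned before the online survey, it is not certain that the baseline questionnaires precede knowledge of allocation. The order of the sentence does not prove otherwise, since the prescription is issued only after the survey, but the plan should settle it.

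**What to change.** Replace the two-step screen with an adjustment set fixed before any outcome data are examined by group:

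- Adjust the primary and secondary analyses for baseline SASKO and at most one or two further named baseline prognostic variables, chosen for their expected relation to the outcome.
- Admit as covariates only values collected before the patient's allocation is known. Reconcile this with Second appointment (baseline assessment) by stating whether the survey is completed before allocation is disclosed.
- State that this pre-specified model governs the conclusion and label any other adjusted analysis as sensitivity.
- Use post-baseline FKK, ADS, PMH and URICA only as outcomes or in analyses labelled as exploratory mediation.
- Drop the exploration of associations with group as a basis for choosing covariates.

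This changes analysis wording only, with no effect on recruitment or data collection. Trial status already provides for updating the protocol in the registry. The one thing given up is the freedom to adjust ad hoc.
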